### *Justification for inclusion criteria:*

1. The intervention targets adult patients with NF1, NF2 and schwannomatosis. Psychoosical Interventions for adults are different than for adolescents. We are currently conducting a preliminary RCT of the 3RP-NF adapted and simplified to the needs of adolescents, via live video.
2. This inclusion criterion will ensure that patients have a thorough understanding of what the study entails and that they are able to provide valid data.
3. The 3RP-NF and HEP-NF manuals have been written to accommodate a 6th grade and higher reading level. This was done in order to accommodate patients with learning disabilities who might have trouble understanding more complex material. Patients who do not meet this criterion (via self-report) will be excluded. During our preliminary RCT, we did not exclude any participants based on this criterion. Further, patients with learning disabilities did not express any concerns about the manual or group sessions.
4. As discussed in the Narrative section, the Relaxation Response Resiliency Program (3RP-NF) is aimed at improving physical and psychological quality of life by improving coping with stress and NF symptoms. As such, the intervention will target patients who report difficulties coping with stress and NF symptoms. The advertising materials will describe that this study is geared toward improving coping with stress and NF symptoms. Further, we will ensure that this inclusionary criterion is met during the individual Skype intake session.
5. The PSS-4 is a valid and reliable measure of stress that will be used to screen for patients who have higher than average levels of stress. By doing so, we ensure that the patients who are at the highest risk are identified and approached.

### *Justification for exclusion criteria:*

1. The presence of a major medical comorbidity not NF related represents an additional huge stressor, which can impact reports and confound results. In our preliminary RCT we had no patients excluded due to this criterion.
2. This exclusion criterion is used to ensure that any intervention effects are due to active ingredients of the intervention, not due to an antidepressant regimen change. In our preliminary RCT we had no patients excluded due to this criterion.
3. The 3RP-NF teaches elements of Cognitive Behavioral Therapy and Relaxation training. This exclusion criterion is meant to ensure that potential gains are due to the 3RP-NF not other interventions. In our preliminary RCT we had no patients excluded due to this criterion.
4. The presence of untreated major mental illness is also an exclusion criterion. Those presenting for

# MIND-BODY SKILLS TRAINING FOR ADULTS WITH NEUROFIBROMATOSIS

participation in the study that need immediate mental health services (e.g., mania, psychotic disorders) will be referred for the appropriate level of care, if that is not already in place. This level of care will be prioritized above their participation in the study. We do not anticipate that many patients will be excluded due to this criterion. In our preliminary RCT, out of 65 participants screened, only 1 was excluded due to this criterion.

5. Because participants will reside across the U.S., electronic data capture is necessary, and we will exclude those unwilling or unable to complete measures electronically. In our preliminary RCT we had no patients excluded due to this criterion.
6. Because the intervention is delivered online via videoconferencing, we will exclude patients not willing or not able to use this medium of intervention delivery. This means that deafened patients will be excluded. The desire for generalizability to all NF patients was balanced with the need to prove the efficacy of the 3RP-NF first. Once efficacy is proven, we will implement caption tools to allow deafened patients to be part of 3RP-NF groups, as part of the dissemination efforts. In fact, we are currently conducting a preliminary RCT of an adapted version of the 3RP-NF in patients with NF2 who are deaf using live video and CART.

## Recruitment

We propose to enroll 224 adults (see power analyses) with NF1, NF2 and schwannomatosis ages 18 and older during the first 3 years of the proposed 4-year project. Active recruitment will be carried out by a trained and experienced research assistant with supervision from the PI. In our current videoconferencing preliminary RCT we recruited through the Children's Tumor Foundation (CTF) NF outreach program, and have received 255 inquiries from interested participants from only 1 email. The CTF is the largest NF nonprofit organization within US. We have commitment from CTF for help with recruitment for the current study (see letter of collaboration). We will also recruit from the Neurofibromatosis clinic at MGH. Flyers will be posted in various areas of the hospital as a recruitment method. Our recruitment video will be posted on the websites of NF groups (e.g., CTF) and on NF-specific social media pages. If needed, we can access other sources of referrals including NCI via [name], Children's Hospital via [name], and John Hopkins Hospital NF Clinic via [name]. We could also buttress recruitment via the NF Facebook group and other available social media mediums. We will also be recruiting by posting our study on Partners Clinical Trials. The Zoom medium allows for recruitment of participants from across the US, making the results generalizable to the NF population. Enrollment and retaining of participants will be buttressed by scheduling the groups in the evenings and weekends, a strategy that allowed for 100% retention in our current preliminary RCT. In our preliminary RCT we enrolled primarily educated participants. This demographic is typically most interested in participation in research. We will make efforts to recruit demographics underrepresented in our current trial through attendance of NF forums and collaboration with CTF (see Human Subjects).

## IV. SUBJECT ENROLLMENT

Participants who express interest will be emailed the study consent form and scheduled for a baseline meeting via Zoom, which includes pre-screening to ensure that participants meet the study criteria, and the consent process (for participants who meet criteria). If needed, members of the research team will contact participants by phone to assist with study-related tasks (e.g., provide technical support to facilitate use of technology). All study staff will participate in National Institute of Health required training for conduct studies that involve human subjects. MGH requires all investigators to pass the Collaborative Institutional Training Initiative (CITI) course and this will be ensured for all study staff. Training for all staff includes but is not limited to Human Subjects, Informed Consent, Good Clinical Practice, Quality Management, Confidentiality and Reporting of Adverse Events.

Justification for using Zoom in this RCT: The decision to use Zoom is based on weighing security of available video conferencing technologies, recommendations by MGH, and consideration of ease of use for participants. Using the Partners Zoom license ensures an end-to-end encrypted video connection, along with the ease of setting meetings to be password-protected. Zoom offers the highest quality video connection, and the easiest installment and use requirements. We believe that Zoom is very user-friendly and will enhance the quality of this RCT through its ease of use.

If as a result of participant self-report, study staff discovery, or routine assessments, the study staff might become aware of self harm; all study staff will be trained to address these issues and the PI will be informed of all such incidences and will personally contact participants to further assess self harm and ensure participant safety. As an additional precaution and consistent with feedback from the 2015 DOD review panel, we will ask all participants

to provide contact information (phone number and email) for at least 1 friend or family member that we can contact in case of emergency. Redcap has the ability to send voice or text messages securely (through “send secure” feature on an encrypted device, and we will program it to send a text to the PI in case a patient endorses the suicidality item (#9 on the PhQ-9) at any of the 4 time points. Should this happen, the PI will immediately contact the patient and/or the friend or family member previously depicted as a safety contact by the participant, and start a safety procedure (assessment, referral, etc) to ensure the safety of the participant. So far during our Skype RCT we have not had any such situations.

## V. STUDY PROCEDURES

Participants will be randomized 1:1 to 3RP-NF or HLI using a permuted-block randomization, stratified by diagnosis. Stratification ensures that an equal number of participants with NF1, NF2 and schwannomatosis are allocated to both treatments. Randomization will be generated by a computer.

We will use the same clinician/study therapist across the study conditions. Consideration was given to using different therapists for each arm to minimize potential contamination. However, observed study effects might be then attributable to clinician/therapist factors, and the study manuals are distinct. To deal with potential contamination, we will employ the audio-recording supervision and review as detailed below, including the use of checklists to document therapist fidelity to the intervention and also to prevent drift.

**1.1. Experimental treatment: The Relaxation Response Resiliency Program for patients with NF (3RP-NF).** The original 3RP program manual was modified to address specific needs of patients with NF, which were identified previously during 2 focus groups (N = 15 participants) and literature review. During these focus groups patients were asked open ended questions about the need for a mind body group, interest in potential participation, difficulties managing NF, and about specific stressors associated with NF1, NF2 and schwannomatosis. Specific modifications included: 1) specific skills aimed at managing NF specific stressors such as burden of medical appointments, dating and difficulties hearing; 2) restructuring NF specific thoughts such as those associated with self image, career, etc; and 3) learning acceptance techniques to address issues associated with making sense of having NF and dealing with the uncertainty of having this condition. The original 3RP manual was modified to address these changes and was used uniformly with each group. Each of the 8 sessions involves a review of previously learned skills, introducing and practicing a new relaxation response technique, and learning a specific cognitive behavioral or positive psychology based skills and applying it to specific patient specific issues. Participants receive 2 relaxation CDs to ease practice at home, as well as a patient manual. Participants are instructed in the importance of practicing the skills at home, and homework forms are collected at the beginning of each session. Further, every session includes discussions on homework completion and problem solving barriers to practice. Groups are small (5-7 participants/group) allowing the facilitator to ensure that patients understand and practice the skills taught. The 3 diagnostic categories are grouped together for the purpose of this study for several reasons. First, there are many similarities among patients with NF1, NF2 and schwannomatosis such as common stressors associated with symptoms (e.g., appearance concerns, pain, uncertainty about progression/growth of tumors, social isolations, concerns about transmission through pregnancy). Second, patients within the 3 categories, as a group, share similar psychosocial difficulties and decreased quality of life. Third, the 3RP is not aimed to target underlying diseases processes, as would a drug; rather, it is aimed at improving coping with stress and symptoms (e.g., increase resiliency) and satisfaction with life. We deal with the heterogeneity of NF by asking patients to set general and weekly practice goals that are specific to them, and teaching them to apply them to their individual goals and concerns. For example, a patient with NF1 who has facial tumors might set a goal of decreasing self-consciousness while a patient with schwannomatosis might set a goal of improving coping with pain. Both patients can benefit from relaxation response strategies as well as from cognitive behavioral and positive psychology skills to help them develop acceptance and an adaptive response to a chronic incurable condition. Lastly, this decision is based on preliminary research. We found no differences in baseline characteristics of patients with NF1, NF2 and schwannomatosis on any of the study variables, with the exception of pain intensity, which was the highest in patients with schwannomatosis. Further, research on the 3RP has shown that patients with various medical and psychiatric concerns respond similarly to the mind body intervention (Gonzalez, [name], & Park, submitted).

**1.2. Time-Matched Attention Placebo Active Comparison Condition: Health Enhancement Program (HEP-NF).** The active comparison condition controls for the effect of “time spent”, “group member support/feedback” and “interventionist support/feedback” and includes delivery of educational information on NF types and symptoms drawn from the CTF website, and standard healthy living information drawn from the Center for Disease Control recommendations and standards for health promotion (e.g., “Sleep”, “Nutrition”, “Healthy Weight”, and “Medical appointments”). These sessions were manualized and used in our preliminary RCT that

## MIND-BODY SKILLS TRAINING FOR ADULTS WITH NEUROFIBROMATOSIS

represents the basis of this research. Such control interventions are routinely used in stringent RCTs of psychosocial interventions. The HEP-NF program consists on 8 group sessions (each session is 90 minutes) that occur concurrently with the active intervention condition 3RP-NF. The active comparison HEP-NF is conducted in the same format as the intervention condition but does not include any relaxation response, cognitive behavioral or positive psychology skills training that are reflected in the 3RP-NF. Patients in the HEP-NF receive the same attention from the study therapist as those in the 3RP-NF.

**6. Protocol integrity.** The integrity of the 3RP-NF and HEP-NF protocols will be assured empirically. All sessions will be audiotaped. We have developed a rating checklist for therapist adherence that includes whether the specific components of each session was in fact delivered. Adherence ratings will be completed by [name]. Competence will be ensured by weekly clinical supervision using audiotapes. At least 20% of the sessions, and at least one session per week, will be reviewed prior to clinical supervision meetings, and the rating checklist will be used to give specific feedback to study therapists.

**7. Strategies to avoid participant unblinding:** Participants will not know whether they are assigned to the 3RP-NF intervention or the HEP-NF control. Rather, they will be informed that they will be randomized to one of 2 stress management groups, in an effort to identify which one works best in patients with NF. In order to prevent unblinding, participants will be asked to not share information discussed in the group on social media sites (e.g., Facebook groups or internet chat groups) or with other NF acquaintances for the duration of the study. We will also explain to study participants how sharing of information would potentially negatively impact the validity of study results. It is important to mention that we have evidence that the HEP-NF control is credible and patients remained generally blind, as we found no differences in scores of satisfaction with overall program at posttest or 6 month follow up. Nevertheless, we anticipate some level of disclosure of techniques from the 3RP-NF groups to the HEP-NF control groups via social media sites, which would make our findings conservative by potentially *underestimating* the true efficacy.

All study assessments will be administered online, using the REDCap system. Subjects consented in person may choose to fill out these questionnaires on-site, or to fill them out at home on a personal computer or other Internet-equipped device. Subjects consented via phone will be asked to complete the questionnaires online, at home. At study intake, participants will be given baseline psychological and behavioral assessments (see attached study questionnaire). This assessment includes demographic information and a battery of psychological questionnaires, itemized below.

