#### I. BACKGROUND AND SIGNIFICANCE

**Neurofibromatoses are prevalent and incurable conditions.** The neurofibromatoses, including neurofibromatosis 1 (NF1), neurofibromatosis 2 (NF2), and schwannomatosis, are a group of genetically distinct disorders of the nervous system unified by the predisposition to nerve sheath tumors. These histologically benign tumors can occur anywhere in the body and often cause significant morbidity including disfiguring cutaneous tumors (NF1); complete hearing loss, facial weakness, and poor gait (NF2); and chronic disabling pain (schwannomatosis). In addition to the increased risk of benign tumors, patients with these genetic syndromes are at higher risk for malignant tumors and can develop non-tumor manifestations that affect the nervous system, eyes, and skin. Currently there is no cure for NF, with symptom management provided by surgery and palliative measures as the primary means of treatment. Neurofibromatosis is the most common genetic neurological disorder that is caused by a single gene, and affects more than 100,000 people in the United States. The recognized prevalence is on the rise due to increased awareness and diagnostic techniques.

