**Study 2: Formative qualitative work informing the adaptation of the 3RP for NF patients (3RP-NF).** The goals of this project were: 1) to determine the need of a mind body intervention for patients with NF, 2) to determine the level of interest in participation in the intervention, and 3) to inform the adaptation of the 3RP to 3RP-NF. We conducted two focus groups (N = 15 participants). Patients were adults with NF1, NF2 and schwannomatosis. They were all in agreement that a mind-body intervention is needed and enthusiastic about participating. Several themes emerged that were unique to this population. Theme 1: social stigmatization. Patients felt that as a group they have been ignored by psychosocial research. They noted general social isolation due to NF related symptoms including: 1) café au lait, freckling or facial tumors in NF1; 2) facial paralyses and deafness in NF2; and 3) pain in schwannomatosis. Theme 2: unique stressors. Generally, patients shared difficulty coping with the following stressors associated with NF: 1) appearance concerns; 2) uncertainty of diagnoses and prognosis (e.g., lack of cure and progression of disease); 3) multiple medical appointments including frequent tests such as MRIs; 4) symptom burden; 5) financial pressure; 6) pregnancy and concerns about transmitting NF to children; and 7) communication with medical providers and dealing with primary care doctors with little knowledge about NF. Theme 3: psychosocial comorbidities. Patients reported that depression and anxiety were main concerns, along with difficulties managing symptoms. When pain was present, difficulties coping with pain were mentioned. Many patients reported that antidepressants and/or pain medications did not relieve their symptoms and some reported a desire to decrease their narcotic medication intake. Conclusion: This study suggested that patients with NF are highly enthusiastic about participation in a mind body program, and helped delineated unique stressors associated with NF to inform the adaptation of the 3RP to 3RP-NF.

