### Inclusion/Exclusion Criteria

Inclusion and exclusion criteria were selected following guidelines for psychosocial treatment development and for bridging efficacy with effectiveness. Women and minorities will not be excluded. Screening will be done through patient self-report either in person (when patients are recruited from the MGH NF clinic) or via Zoom (when patients are recruited through CTF).

| Inclusion Criteria                                                    | Exclusion Criteria                                                                       |
|-----------------------------------------------------------------------|------------------------------------------------------------------------------------------|
| 1. Has a diagnosis of NF1, NF2 or schwannomatosis and is 18 or older. | 1. Has major medical comorbidity not NF related expected to worsen in the next 12 months |

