### VII. RISKS AND DISCOMFORTS

Patients will be informed that there are no foreseeable physical risks from this research study. They will be informed that they may feel uncomfortable completing various psychological questionnaires and that they may find it time-consuming to participate in weekly 90 minute groups.

As Zoom is HIPPA approved and secure, there are no risks associated with its use. However, patients will be asked to ensure that they are in a private room during the group sessions, to protect their privacy and that of group members.

As with any group studies, there may be confidentiality issues, but we will discuss the importance of maintaining confidentiality at the beginning of each group.

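### The safeguards against contamination and unblinding do not cover adults with NF who share a household and can be randomised to opposite arms

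*Protocol*

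**What the plan says.** **Who may enrol.** The first inclusion criterion (section III, Inclusion/Exclusion Criteria) is "Has a diagnosis of NF1, NF2 or schwannomatosis and is 18 or older". None of the other inclusion or exclusion criteria mentions relatives or shared households.

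**How they are allocated.** Section V: "Participants will be randomized 1:1 to 3RP-NF or HLI using a permuted-block randomization, stratified by diagnosis". HLI here is the control that the rest of section V calls HEP-NF. The unit is the individual and diagnosis is the only stratum. No rule deals with people who live together.

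**What goes into the home.** Section V, item 1.1, on the 3RP-NF arm: "Participants receive 2 relaxation CDs to ease practice at home, as well as a patient manual". Participants are also told to practise at home and to hand in homework.

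**What protects the contrast.** Section V, item 7 has three elements: both programmes are presented neutrally as stress management groups, participants are asked not to share group content on social media "or with other NF acquaintances for the duration of the study", and they are told why sharing would harm the results. Section VII adds that "patients will be asked to ensure that they are in a private room during the group sessions", for the sake of privacy. Item 7 concedes that "we anticipate some level of disclosure of techniques from the 3RP-NF groups to the HEP-NF control groups via social media sites" and regards the consequence as conservative.

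**Why relatives are foreseeable.** Section I calls the neurofibromatoses "a group of genetically distinct disorders of the nervous system", and the focus groups (Study 2) list "pregnancy and concerns about transmitting NF to children" among the stressors.

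**The concern.** In a heritable disease recruited through one specialist clinic and one patient foundation, two affected adults from the same home are a foreseeable pair of applicants. If they are split, the HEP-NF member lives with the relaxation recordings, the manual and someone practising the skills that the control programme is built to leave out.

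The sharing request concerns what is discussed in the group, and the private-room request concerns live sessions. Neither reaches materials and practice in a shared home. The only route of leakage that item 7 names is social media.

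At stake is dilution of the difference on two self-reported co-primary outcomes. Physical QoL is planned at 80% power, so it has little to give away. Unlike social media, this route can be closed at enrolment.

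**Working it through.** **Inputs from the protocol (section VI, items 1, 3 and 3.1).** Difference 6.25 units; effective SD of change 14.7 (Physical) and 10.4 (Psychological); two-sided 0.025 per outcome; 224 enrolled, at least 212 at post-treatment, so 106 per arm.

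**The plan's own figure.** The standard error for Physical QoL is 14.7 × √(2/106) = 2.019, so the noncentrality is 6.25 / 2.019 = 3.095. Against the critical t of 2.258 on 210 degrees of freedom, power is 79.8% (80.3% by the normal approximation). The stated 80% reproduces. The same calculation for Psychological QoL gives 98.2%, above the stated 96%. That value appears at about 90 per arm (96.1%). The gap is in the safe direction and does not affect this point.

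**Dilution model (assumptions).**
- f = share of participants who live with another participant. Not given; taken as 2% to 20%.
- s = probability that a pair is split. It is 0.5 if the two fall in different blocks. If they fall in the same block of size b it is (b/2)/(b − 1), that is 2/3 for b = 4 and 3/5 for b = 6.
- c = share of the treatment contrast lost in a split pair. Not given; taken as 0.5, with 1.0 as the upper bound.

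A fraction f × s of the HEP-NF arm has a housemate in 3RP-NF, so the expected difference is 6.25 × (1 − f × s × c).

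**Results with s = 0.5 (noncentral t, 106 per arm).**

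| f | Split pairs among 224 (224 × f / 2 × 0.5) | Difference, c = 0.5 | Physical power | Difference, c = 1.0 | Physical power |
|---|---|---|---|---|---|
| 2% | 1.1 | 6.22 | 79.4% | 6.19 | 79.0% |
| 5% | 2.8 | 6.17 | 78.7% | 6.09 | 77.6% |
| 10% | 5.6 | 6.09 | 77.6% | 5.94 | 75.2% |
| 20% | 11.2 | 5.94 | 75.2% | 5.63 | 70.1% |

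The normal approximation gives values about half a point higher.

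**Stratification does not help.** Related housemates would normally share a diagnosis and hence a stratum. If they enrol close together they may share a block, which raises s above one half. With s = 2/3 and c = 0.5, Physical power at f = 5%, 10% and 20% is 78.4%, 76.8% and 73.6%. The extreme corner (f = 20%, c = 1.0) gives 66.5%.

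**Psychological QoL.** With s = 0.5 the lowest value is 95.3%. In the extreme corner it is 93.7%.

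**The case against.** The case against rests on five arguments.

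- **No evidence of such pairs.** A worry about passing NF to children does not show that two affected adults share a home, both volunteer, and both meet the stress and coping criteria. The account of the videoconference pilot mentions no related participants. This stands: the trial-wide effect may be negligible.
- **There are safeguards.** A relative with NF can be read as an acquaintance with NF, the framing is neutral, the reason for discretion is explained, and a private room limits overhearing. This stands as far as it goes. A reader might infer that a split household defeats the safeguards, or that the sharing request is the only one; the text supports neither. What remains is that none of these measures covers materials and practice in a shared home.
- **Blinding.** A reader might infer that a split pair is unblinded by learning that the programmes differ. Every participant is already told that there are two programmes under comparison. What is masked is which one is the control, and differing content does not by itself reveal that. Easier guessing is possible but not shown.
- **Total loss of contrast is extreme.** It would mean that recordings and a manual in the house deliver the benefit of eight group sessions. Agreed, so it is given only as a bound. Nor do the documents say that practice is daily, and the calculation does not assume it.
- **Leakage is conservative.** Leaked skills bias toward no difference. That is right for the direction of this dilution, but it still costs power on the outcome with least to spare.

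**Conclusion.** The gap is real and minor. Nothing in the protocol prevents one household from being split between arms, and the safeguards do not address that case. Under the central assumptions (half of pairs split, half of the contrast lost in them), Physical QoL power falls from about 80% to about 79%, 78% or 75% when 5%, 10% or 20% of participants share a household. Total loss of contrast gives about 78%, 75% or 70%. At 2% the cost is about one point or less. Psychological QoL is hardly affected.

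The share of participants in common households and the transfer of benefit are both assumptions, so these figures show a range and do not predict a loss. The model counts only people who live together; relatives in separate homes are not exposed by this route and should not be added in. No false positive result is implied.

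**What to change.** At the pre-screening in the baseline meeting, ask whether a household member is in the study or is applying to it, and record the answer. Add a criterion that one person per household is enrolled.

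If two members apply together and both are to be included, randomise them as one unit before either allocation is known, and account for the pair in the mixed model. A later applicant should not simply be placed in the arm of a housemate already enrolled: that allocation would be known in advance, which gives up both concealment and randomisation for that person.

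The cost is one screening question, one criterion and a few lost enrolments. The Recruitment section reports 255 inquiries from a single email in the pilot, against a target of 224 here, so that loss looks bearable, although some eligible people with a rare disease would be turned away. The joint-randomisation option costs slightly looser balance within diagnosis and an extra term in the model.
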